## Sample size calculation

Based on hepatic PNPLA3 expression that is twice as high in steatosis patients compared to healthy obese subjects (Aragonès et al., 2016). To detect a 25% reduction in PNPLA2 expression upon 12 weeks exercise course, we expected to need a group sample size of 28 (2sided chi- square test with a desired alpha of 0.05 and a desired power of 0.8). Assuming around 10 % of dropouts in this trial, a final sample size of 30 is required. Based on the suggestions of the IRB we will start with inclusion of 15 subjects and study changes in liver gene RNAseq including PNPLA3 gene liver expression upon exercise (Aragonès et al., 2016). Based on those findings, we will validate our power calculation above and see if the number of 30 subjects is indeed needed.

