**Objective**: We aim to study the effect of exercise on NAFLD (by analysing hepatic lipid content, liver histology, and gene expression). Furthermore, we aim to establish the role of exercise-mediated changes in gut microbiome in the reduction of severity of NAFLD and the relation with other metabolically involved organs including adipose tissue and muscle metabolism and glucose excursions. We thus aim to identify biomarkers of exercise effect on NAFLD state. These biomarkers comprise plasma and urine metabolites, gene expression of liver, muscle and adipose tissue, as well as gut microbial composition.

**Study design:** Intervention study.

**Study population:** In total 15 subjects aged 18-70 years of age with diagnosed NAFLD.

**Intervention (if applicable)**: High-intensity interval exercise training for 12 weeks.

**Main study parameters/endpoints:** The main study parameters are changes in NAFLD liver histology and gene expression in relation to oral and gut microbiota composition changes upon exercise. Second changes in other organs involved upon exercise driven metabolic fitness including subcutaneous adipose tissue and muscle gene expression (RNA-sequencing) and histology, in relation to glucose metabolism (freestyle libre) and metabolites in plasma and urine will be studied. Finally, the relative contribution to NAFLD and glucose metabolism of the different organs (liver, adipose tissue and muscle) upon exercise will be studied.

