## Replacement of individual subjects after withdrawal

Withdrawn subjects will be replaced in order to attain the desired sample size.

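### Section 4.4 claims 80% power with 28 subjects, but the figure cannot be derived: the test does not fit the outcome, no SD or proportions are given, and two genes are named

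*Protocol*

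**What the plan says.** All the inputs to the calculation stand in protocol section 4.4.

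- Empirical basis: "Based on hepatic PNPLA3 expression that is twice as high in steatosis patients compared to healthy obese subjects". This is a comparison between patient groups.
- Target and size: "To detect a 25% reduction in PNPLA2 expression upon 12 weeks exercise course, we expected to need a group sample size of 28".
- Test and error rates: "2sided chi- square test with a desired alpha of 0.05 and a desired power of 0.8".
- Allowance for loss: "Assuming around 10 % of dropouts in this trial, a final sample size of 30 is required".
- Interim check: begin with 15 subjects and "study changes in liver gene RNAseq including PNPLA3 gene liver expression upon exercise", then validate the power calculation and decide whether 30 are needed.

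Elsewhere, section 6.1.1 makes gene expression by RNA sequencing a main endpoint, from biopsies at baseline and endpoint. Sections 3 and 6.2 describe one group without randomisation. Section 8.1 plans a one-sample t-test or a chi-square test between baseline and endpoint. Section 6.5 adds: "Withdrawn subjects will be replaced in order to attain the desired sample size".

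**The concern.** A percentage fall in gene expression within the same subject is a continuous paired change. To size a study for it, one needs the SD of that change. A chi-square test needs proportions instead. Section 4.4 has neither, so the step from a 25% reduction to 28 subjects is missing. The two-fold difference between patient groups does not fill the gap, because it carries no information on how much expression varies within a subject over 12 weeks.

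The gene also changes within the paragraph: PNPLA3 in the rationale, PNPLA2 in the target effect, PNPLA3 again at the interim check. This may be a typing error, but it sits in the definition of the effect being powered.

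The number matters because it feeds the study's one adaptive decision. The results in the first 15 are to be held against this calculation, and the ethics board would be asked to approve up to 15 more subjects, each facing liver, muscle and fat biopsies. A power statement without its inputs gives that decision a poor reference point.

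**Working it through.** **Inputs.** Two-sided alpha 0.05, power 0.80, 25% reduction, n = 28, dropout about 10%, 30 enrolled (all section 4.4). Paired, single-arm data (sections 3, 6.1.1, 6.2). SD of change and proportions: not stated, so every value below is an assumption.

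**Step 1: can 28 be reproduced with a chi-square test?** Only by supplying proportions that the protocol does not give.

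- Two groups, 100% v 75%: n per group = [1.96 × √(2 × 0.875 × 0.125) + 0.842 × √(0.75 × 0.25)]² / 0.25² = 26.3, so 27 per group.
- Two groups, 50% v 25%: 57.7, so 58 per group.
- One group, 50% v 25%: [1.96 × 0.5 + 0.842 × √(0.25 × 0.75)]² / 0.25² = 28.9, so 29.
- General effect size: n = 28 corresponds to w = √[(1.96 + 0.842)² / 28] = 0.53.

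The results of 27 and 29 come close to 28, but they rest on invented proportions, and the two-group versions do not fit a single-arm study.

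**Step 2: what does 28 imply with a paired t-test?** Power comes from the noncentral t distribution with n − 1 degrees of freedom and noncentrality d√n, where d = 25% / SD of change (SD as a percentage of mean baseline expression). Solving for 80% power at n = 28 gives d = 0.549, hence SD = 25 / 0.549 = 45.5% of baseline. This value is back-solved from 28 and has no source in the protocol.

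**Step 3: how much does the missing SD matter?**

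| Assumed SD of change (% of baseline) | n for 80% power | Power at 15 | Power at 27 | Power at 28 |
|---|---|---|---|---|
| 30 | 14 | 85.1% | 98.6% | 98.9% |
| 40 | 23 | 61.5% | 87.8% | 89.0% |
| 45 | 28 | 51.7% | 79.4% | 80.9% |
| 50 | 34 | 43.8% | 70.6% | 72.3% |
| 60 | 48 | 32.4% | 55.0% | 56.6% |
| 75 | 73 | 22.5% | 38.5% | 39.8% |

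These figures hold on the relative scale only. On a log2 scale the target is log2(0.75) = −0.415, and the SD must be assumed on that scale separately. The two kinds of SD are not interchangeable.

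**Step 4: dropout.** 30 × 0.90 = 27. Keeping 28 needs 28 / 0.90 = 31.1, so 32 enrolled. Thirty enrolled keeps 28 only if the loss is at most 2/30 = 6.7%. At d = 0.549, 27 completers give 78.4% power against 80.0% for 28, a loss of 1.6 percentage points.

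**The case against.** The strongest reply is that chi-square is not foreign to this plan. Section 8.1 lists it beside the one-sample t-test, the main endpoints include histology, which can be categorical, and a one-sample comparison of 50% with 25% gives 29. That stands so far as this: a reader should not infer that no chi-square calculation could give a number near 28. It does not rescue section 4.4, which describes a reduction in expression and states no responder definition or proportion.

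A second reply is that the design corrects itself. The first 15 pairs can supply the missing SD, and the need for 30 is conditional on them. This limits the consequence, and it would be too strong to say that the interim has nothing to work with. It does not supply the inputs behind the power stated now.

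Third, the dropout shortfall is small. The text says around 10%, the cost is 1.6 points under the implied effect size, and replacement under section 6.5 largely removes it. That is right, so the point is secondary. Allowance plus replacement is an overlap to tidy up and hardly a contradiction.

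A reader might also infer that the study is underpowered. The documents do not support that: at an SD of 30%, 14 subjects would do. Nor does the Summary's "In total 15 subjects aged 18-70 years of age with diagnosed NAFLD" promise 80% power for 15. Sections 3 and 4.4 explain the staging, and the 0.8 is attached to 28.

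**Conclusion.** The 80% power attached to 28 subjects is unsupported as written. Three defects carry this: a chi-square test cited for a continuous paired change, no SD of change or proportions, and a target effect on a different gene from the rationale and interim check. Whether 28 is too few, adequate or generous depends on an SD that the protocol does not give. Over assumed SDs of 30% to 75% of baseline, power at 28 runs from 99% down to 40%, and it is 80% only near 45%. These figures assume a paired t-test at two-sided 0.05, a 25% mean reduction and roughly normal changes on the relative scale. The mismatch between 30 enrolled and 28 evaluable is real but minor.

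**What to change.** Rewrite section 4.4 as follows.

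1. Size the study for the planned one-sample (paired) t-test on within-subject change, on one stated scale, for example log2.
2. Reconcile the gene name. The sponsor should confirm which gene was meant; the document shows only the mismatch.
3. State the SD of change as an explicit assumption with its source. Do not adopt an SD because it reproduces 28; that would be circular.
4. Replace the unconditional 80% claim with power over a range of SDs, on the chosen scale, for 15, 27 and 28 evaluable subjects.
5. Keep one rule for losses: either the allowance (30 enrolled, 27 evaluable) or replacement under section 6.5.
6. State that the SD of change observed in the first 15 pairs, with the 25% target held fixed, will be used to re-check whether 30 are needed.

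The cost is one rewritten paragraph and a matching edit to section 6.5 if the allowance is kept. The stated power becomes conditional and may look less favourable. No extra patients are required.

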# TREATMENTS OF SUBJECTS

## Treatment

The intervention group will follow a high-intensity interval training (HI) protocol on a cycle ergometer (Hallsworth et al., 2015). To determine the intensity of the individually prescribed training program and the efficacy of the exercise intervention, ergospirometry tests will be performed in collaboration with the department of Cardiology AMC ([name]) that has all expertise to execute this study. The training sessions and ergospirometry tests will be carried out in Polifysiek, Hogeschool van Amsterdam. Furthermore, physical activity of study subjects will be monitored through the intervention by questionnaires. These are described later in the chapter of study procedures. Subjects are asked to keep their diet and weight unchanged.

The exercise intervention will start immediately after the ergospirometry test. In detail, the concept of HI involves repeated bouts of exercise at an intensity of 85 % of W_max4_ interspersed by recovery periods based on a baseline ergospirometry test. W_max4_ refers to the hypothetical workload sustainable for 4 min (Tornvall G, 1963). While being hypothetical, W_max4_ is useful for defining the presumably optimal intensity for work intervals at HI. The intervention group will perform HI session involving 5 bouts of 2-4 minutes work intervals (at 85 % of W_max4_) interspersed by 3 minutes of active recovery (at 10 % of W_max4_) period twice per week on non-consecutive days for 12 weeks. Each work interval will be 2 minutes long in the first week with 5 seconds added per each exercise session (i.e. 10 seconds per week) so that HI intervals will be 4 minutes long by week 12. If the subject fails to complete the work interval, he/she will still be instructed to continue the exercise session by starting the following scheduled work interval(s) after the recovery period(s). At the beginning of the intervention period, each HI session will last approximately 40 minutes, including warm-up (at 30% of W_max4_), recovery periods and cool-down (at 20 % of W_max4_). At the end of the intervention period, each HI session will last approximately 50 minutes. HI will be conducted in a group of 1-3 subjects closely supervised by exercise physiologist, or some other qualified health care professional (e.g. biomedical laboratory scientist) adequately trained for the task.

Additionally, an individualized exercise training program will be prescribed for each subject in the HI group consisting of home-based low-to moderate-intensity aerobic exercises. An overall weekly goal, including supervised exercise, will be three hours of aerobic exercise e.g. walking, swimming and cycling following international guidelines (US GUIDELINE 2018). Exercise training program is described in details in table 1.

Table 1. Exercise training program in high-intensity aerobic interval group.

| Study weeks | **0–4** | **5-8** | **9-12** |
| --- | --- | --- | --- |
| *High-intensity aerobic interval training* |  |  |  |
| Duration of warm-up, min | 10 | 10 | 10 |
| High-intensity interval training frequency/week | 2 | 2 | 2 |
| Intensity of work phase, % W_max4_ | 85 | 85 | 85 |
| Intensity of recovery phase, % W_max4_ | 10 | 10 | 10 |
| Interval sets, number | 5 | 5 | 5 |
| Duration of the interval, seconds | 120-160 | 160-200 | 200-240 |
| Recovery between sets, minutes | 3 | 3 | 3 |
| Intensity of warm-up, % W_max4_ | 30 | 30 | 30 |
| Intensity of cool-down, % W_max4_ | 20 | 20 | 20 |
| Duration of cool-down, min | 5 | 5 | 5 |
| *Additional home-based aerobic training* |  |  |  |
| Duration, min/week | 140 | 120 | 100 |

W_max4_ refers to the hypothetical workload sustainable for 4 minutes.

# METHODS

## Study parameters/endpoints

### Main study parameter/endpoint

Main study parameters and endpoints include:

- NAFL disease progression, evaluated by liver biopsy and MRI/MRS scan. This is based on analysis between baseline and endpoint.
- Hepatic, muscle and adipose tissue histology and gene expression (evaluated by RNA-sequencing) that is affected by exercise intervention. This is based on liver, muscle and adipose tissue biopsy at baseline and endpoint.

### Secondary study parameters/endpoints (if applicable)

Secondary study parameters include:

- Fecal and oral microbial composition, evaluated by metagenomic sequencing. This is based on oral and fecal sample at baseline, midway and endpoint.
- Metabolite quantification of plasma and urine samples. This is based on urine samples at baseline and endpoint, and blood samples at baseline, midway and endpoint.
- Gut motility in NAFLD patients. This is based on motility MRI analysis at baseline and endpoint.

### Other study parameters (if applicable)

Other study parameters include:

- Body weight will be measured at baseline, mid-intervention and final study visits to include as possible confounding factors.
- Body composition will be measured at baseline and final study visits to include as possible confounding factors.
- Physical activity will be followed by questionnaire.
- REE will be determined at baseline and endpoint.
- Dietary intake lists will be screened before baseline, mid-intervention and final visits to see whether there is changes in dietary habits as possible confounding factor.
- Relative contribution of (RNAseq metabolic pathway based) metabolic changes in each organ (liver/muscle/adipose tissue) and gut microbiota (metabolic pathway) metabolic changes in relation to exercise induced glucose metabolism improvements.
- Calf circumference will be determined at baseline and endpoint.
- Pre- and postexercise blood biomarkers.

## Randomisation, blinding and treatment allocation

Not applicable.

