# STUDY DESIGN

This study is designed as an intervention study in which subjects will follow the 12-week exercise intervention. Subjects will receive instructions for a high-intensity aerobic interval training (HI) (described below). Dietary intake will remain unchanged. The first part of the study is conducted with 15 subjects. This is followed by an interim analysis and based on the results of this analysis, the intervention will be extended with another 15 subjects based on approval by the IRB. The study design is presented in figure 1.

Complementary study

Baseline

Mid-intervention

Final intervention

Interim analysis

Diagnosed NAFLD

(5.5 % > liver fat)

BMI < 40 kg/m^2^

18–70 years of age

n=15

Ergospirometry test

Anthropometrics

Food records

REE

Oral swab

Stool and urine samples

MRI and MRS

Blood samples

Liver, adipose tissue and muscle biopsies

Ergospirometry test

Anthropometrics

Food records

REE

Oral swab

Stool and urine samples

MRI and MRS

Blood samples

Liver, adipose tissue and muscle biopsies

Body weight

Food records

Oral swab

Stool samples

Blood samples

Exercise intervention – pilot study

Screening

Week 0

+/- 3 week

Identical to pilot study,

recruitment of

additional subjects

+/- 3 months

Continous glucose monitoring

Continous glucose monitoring

Week 12

+/- 3 week

Week 6

+/- 2 week

Figure 1 Overview of the study design with the main procedures that will be performed during the 12-week exercise intervention.

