# STATISTICAL ANALYSIS

## Primary study parameter(s)

Statistical analyses will be performed by SPSS statistical analysis software. Normality of the data will be assessed by a Kolmogorov–Smirnov test. Data transformation will be done if the data is not normally distributed. The primary analyses of studied primary parameters will be performed between the baseline and endpoint intervention by analysis of one-sample t-test, or chi-square test. If the data is not normally distributed and data transformation is not possible, the Mann-Whitney test will be used. Further associations will be assessed with Pearson rank correlation test / Pearson chi-square test.

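### Blinding is declared not applicable, which is right for treatment allocation but leaves the before-after reading of histology and reader-dependent MRI unprotected in a study with no control group

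*Protocol*

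**What the plan says.** Section 6.2 of the protocol combines three topics under one heading, "Randomisation, blinding and treatment allocation", and answers all of them with "Not applicable".

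Section 3 describes one group: "This study is designed as an intervention study in which subjects will follow the 12-week exercise intervention". There is no comparison arm.

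Section 6.1.1 names two main endpoints. The first is "NAFL disease progression, evaluated by liver biopsy and MRI/MRS scan", and the protocol adds: "This is based on analysis between baseline and endpoint". The second begins "Hepatic, muscle and adipose tissue histology and gene expression (evaluated by RNA-sequencing" and draws on biopsies at the same two visits.

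Section 8.1 says that the primary analyses "will be performed between the baseline and endpoint intervention by analysis of one-sample t-test, or chi-square test".

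The procedure sections for MRI, MRS, transient elastography and the three biopsies (6.3.7 to 6.3.9 and 6.3.13 to 6.3.15) do not mention masking to visit, coded or random reading order, paired reading, or a second or central reader. Section 10.1 gives the data a study code for each subject.

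**The concern.** Whether a subject was randomised and whether a reader knows the visit are separate questions. Without randomisation there is no allocation to conceal, but each subject still has two biopsies and two scans, and the difference between the two readings is the result. Histology is a human judgement, and so are some measures taken from MRI.

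In a controlled trial, a drift in reading between the first and last visit would largely cancel between the arms. Here nothing subtracts it: a systematic reading difference between visits passes in full into the estimated change, and the analysis attributes it to exercise. Adding subjects does not help. It narrows the standard error around a biased mean, so the possible extension from 15 to 30 subjects makes a false positive from a fixed shift more likely.

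**Working it through.** **1. Does any other part of the protocol supply the protection?**

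- *Imaging and biopsy procedures (6.3.7 to 6.3.9, 6.3.13 to 6.3.15).* They cover acquisition and storage. They do not say how specimens or scans are labelled, ordered or timed for reading.
- *Study code (10.1).* It protects identity. Nothing says that it hides whether a sample is from before or after the intervention.
- *Use of the baseline biopsy (Summary).* A finding of NASH at baseline leads to clinical referral, so a baseline reading is made and acted on during the study.
- *Earlier biopsies (6.3.13).* A biopsy from the 12 months before screening can stand in for the baseline biopsy, so some baseline specimens may have been reported before the study began.

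The last two points make separate readings of the two visits a realistic outcome of the current text. Nothing found reverses the answer in 6.2.

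**2. Which main endpoints are exposed?**

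| Measure | Role in protocol | Open to reader expectation? |
|---|---|---|
| Liver, muscle and adipose histology | Main (6.1.1) | Yes |
| MRI measures that need a reader's judgement | Main where they inform disease progression (6.1.1) | Yes, as far as a reader decides |
| MRS liver lipid | Main (6.1.1), quantified (6.3.8) | Partly |
| RNA-sequencing expression | Main (6.1.1) and basis of the sample size (4.4) | Little; instrument-read |
| Gut motility on MRI | Secondary (6.1.2) | Outside this point |

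**3. How much could it matter? (illustration only)**

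The protocol gives no figure to reproduce. Inputs from the protocol are the one-sample t-test (8.1), two-sided alpha of 0.05 (4.4), n=15 for the first part (3) and n=28 before dropout (4.4). The assumption is a true change of zero and a systematic reading shift of b standard deviations of the change score, with b from 0.1 to 0.25.

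Under that assumption the t statistic has a noncentral t distribution with n-1 degrees of freedom and noncentrality b√n. The false-positive rate is P(|T| > critical value).

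| n | Critical value | b | b√n | False-positive rate |
|---|---|---|---|---|
| 15 | 2.145 | 0.1 | 0.387 | 6.5% |
| 15 | 2.145 | 0.25 | 0.968 | 14.7% |
| 28 | 2.052 | 0.1 | 0.529 | 8.0% |
| 28 | 2.052 | 0.25 | 1.323 | 24.8% |

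With b=0 the rate is 5.0% at either size.

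**The case against.** The strongest reply is that section 6.2 is a combined heading, that its natural subject is blinding to treatment, and that for one group the answer is then correct. Reading procedures may also sit in a pathology or imaging manual that is not at hand. The storage sections keep samples until analysis, so deferred, paired reading is compatible with the text.

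Part of this stands. A reader might infer that assessors will know which specimen is post-exercise. The protocol does not say so; it says nothing about labelling or order of reading. The supportable statement is that nothing in it prevents this. The reply still does not rescue the answer in 6.2: the section is where blinding is settled, it dismisses the topic as a whole, and who reads what under which label is a matter of trial conduct rather than a detail of a statistical analysis plan.

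A reader might also infer that all main endpoints are compromised. They are not. RNA-sequencing expression, the only endpoint behind the sample size, is instrument-read, and MRS lipid is largely quantified.

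The figures are open to challenge too, and fairly. The shift sizes have no source in the protocol. The 28 was derived for gene expression, the endpoint least open to a reader's expectation. No histology score is named; for an ordinal score, section 8.1 would permit a chi-square or rank test, and the t-test rates would then not apply directly. The rates should not carry the weight of the point.

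Finally, masking is not free, because baseline biopsies are read clinically first. That affects the cost of the remedy, not the need for it.

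**Conclusion.** The point holds in a limited form. The protocol's answer on blinding is right for randomisation and allocation and wrong for outcome assessment. For histology in three tissues and for reader-dependent MRI measures, reader expectation or drift cannot be told apart from the effect of exercise, because the comparison is within subject and has no control group.

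This conclusion rests on the text alone: the answer in 6.2, the main endpoints in 6.1.1, the single-group design in section 3, and the absence of masking elsewhere. Its size is unknown. Under the assumed shifts of 0.1 to 0.25 SD, the nominal 5% error rate becomes roughly 7-15% with 15 subjects and 8-25% with 28. The protocol should be changed, since the remedy is simple and the design has no comparison arm to absorb the bias.

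**What to change.** In section 6.2, keep the present answer for randomisation and treatment allocation, and add a statement on outcome assessment along these lines:

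- For the research scores, both histology specimens and both scans of a subject carry codes that do not reveal the visit.
- The two are read in the same session, by the same reader, in random order, without visit label or date.
- The codes are broken only after the scores are locked.
- The clinical report of the baseline biopsy, which serves the referral described in the Summary, stays as it is and is separate from the research score.

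**Cost.** The change adds no visit or procedure for subjects and needs no extra staff. It does require recoding, and a second, masked research reading of baseline biopsies already reported clinically, including earlier biopsies accepted under section 6.3.13. Baseline research scores become available only after week 12.
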